### Sample size *{14}*

Sample size was estimated using a target power of 80%, at a type I error rate of 0.05, and was calculated relative to the primary outcome measure; distress rating on the 11-point Distress Thermometer (DT) scale. The statistical test assumed was an independent samples *t*-test for group differences in the change from baseline to subsequent assessment, assuming that the randomisation ensures no systematic baseline or other covariate group differences. The minimal clinically significant difference for the DT is estimated to be 1 unit (standard deviation of improvement of 2 units), similar to other 11-point Likert scale questionnaires [30]. Calculation produced a suggested sample size of 64 per group. Allowing for a potential attrition rate of 20%, our final sample size is 80 participants per group (8 groups of 10).

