### Statistical methods

#### Statistical methods for primary and secondary outcomes *{20a}*

Outcome analyses will be performed by a dedicated biostatistician. An intention-to-treat analysis will be performed on all randomised patients and a per-protocol analysis will be performed on all patients who complete the study. Descriptive statistics will be calculated for all outcome measures at each time point. Continuous variables will be reported using means, medians, standard deviations and score ranges. Categorical variables will be described using frequencies and percentages.

Descriptive and inferential statistics will be obtained using the appropriate statistical methods that seek to address our identified objectives. The primary analysis will compare the effect of the interventions on the primary outcome; distress levels at 12 weeks post-completion of the intervention period (i.e. c18 weeks post-baseline). All outcome analyses will be conducted according to an intention-to-treat principle, i.e. all randomised participants will be included in the main analysis and will be analysed as randomised, regardless of protocol adherence. Secondary analysis will include the analysis of the primary outcome post-intervention and analysis of the secondary and treatment process outcomes detailed previously post-intervention and at the 12-week follow-up. Linear mixed models on the outcome measures over time will be fitted to evaluate the effect of both study conditions, which intrinsically adjusts for baseline scores.

Statistical significance will be assessed from a *p* value < 0.05 from the group by time interaction term. For all tests, two-sided *p* values will be used, which will be reported to four decimal places with *p* values < 0.001 reported as *p* < 0.001. The Bonferroni method will be used to appropriately adjust the overall level of significance for multiple secondary outcomes as applicable. In the case of a significant result, planned contrasts of the group effects at the post-treatment period and at the 12-week follow-up will be used to investigate the direction and pattern of effects and outlined in advance in the SAP. As a key component of the reporting of the analyses of outcomes, the mean changes (irrespective of statistical significance) and correlations of the measures between the assessment time periods will be obtained. SPSS will be used to conduct the analyses.

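### Significance is decided by the group-by-time interaction over three visits, while the primary endpoint and the sample size concern a single 18-week difference

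*Protocol article*

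**What the plan says.** The statistical methods section {20a} names one time point for the primary analysis: "The primary analysis will compare the effect of the interventions on the primary outcome; distress levels at 12 weeks post-completion of the intervention period", which it equates with about 18 weeks from baseline. The DT result straight after the intervention is listed there as a secondary analysis. The Abstract, Trial design {8} and Outcomes {12} give the same primary time point.

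The same section then says that linear mixed models will be fitted to the outcomes over time and that significance will be read from the group-by-time interaction at p < 0.05. The contrasts follow under a condition: "In the case of a significant result, planned contrasts of the group effects at the post-treatment period and at the 12-week follow-up" are to be used to explore the direction and pattern of effects, with details in the SAP. Data collection {18a} gives three assessments: baseline (t0), week 6 (t1) and 12 weeks later (t2).

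Sample size {14} rests on an independent-samples t-test "for group differences in the change from baseline to subsequent assessment". That is one change compared between two arms, so one degree of freedom. The section does not say which later assessment is meant, but it is a single one.

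**The concern.** An interaction over three visits asks whether the arms differ in their course anywhere after baseline. The primary question is whether they differ at 18 weeks. The two can part company in both directions. A benefit at week 6 that has gone by 18 weeks can meet the stated criterion. A real 18-week difference may never be formally tested because the interaction missed 0.05. The 80% power in the sample size section also belongs to a test other than the one that decides significance. At stake is what the trial may claim as its main result.

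**Working it through.** **The plan's own figure.** Inputs from Sample size {14}: "Sample size was estimated using a target power of 80%, at a type I error rate of 0.05"; difference 1 unit, SD of change 2. From {20a}: "For all tests, two-sided".

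- Normal approximation: n = 2 × (1.960 + 0.842)² × 2² / 1² = 62.8, so 63 per group.
- Exact t-test: 63.77, so 64 per group, with power 80.1% at 64 (80.7% by the normal approximation).
- Attrition: 64 / 0.80 = 80.

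The stated 64 and 80 reproduce. A one-sided test would need only 50, so the plan's calculation is two-sided.

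**The interaction test.** The document gives no week-6 effect, no correlation between the two changes and no coding of time. Assumptions: time as a three-level factor, SD of change 2 at both visits, correlation r = 0.3, 0.5 or 0.7, week-6 effect 0 to 1.5 units. The interaction is then a 2-df test of the effect vector d = (d1, d2) for t1 and t2, with noncentrality

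λ = (n/2) d′Σ⁻¹d, Σ = 4 × [[1, r], [r, 1]].

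With n = 64 this reduces to λ = 8 (d1² − 2r·d1·d2 + d2²) / (1 − r²). Two examples at r = 0.5:

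- d = (1, 0): λ = 8 / 0.75 = 10.67
- d = (0.5, 1): λ = 8 × 0.75 / 0.75 = 8.0

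Interaction power below uses the noncentral F with 2 and 125 df. The joint probabilities use 400,000 simulated draws per scenario with normal and chi-square limits; on that scale the ungated 18-week contrast has 80.7% power. Cells give r = 0.3 / 0.5 / 0.7.

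| Effect at t1, t2 | Interaction significant (%) | Interaction and 18-week contrast both significant (%) | 18-week contrast significant but blocked by the gate (%) |
|---|---|---|---|
| 1, 0 | 75 / 83 / 95 | 4.9 / 4.9 / 5.0 | 0.1 / 0.1 / 0.0 |
| 0, 1 | 75 / 83 / 95 | 72.9 / 76.7 / 80.1 | 7.9 / 4.1 / 0.7 |
| 0.5, 1 | 73 / 71 / 74 | 71.7 / 70.5 / 72.5 | 9.1 / 10.2 / 8.2 |
| 1, 1 | 88 / 83 / 78 | 78.3 / 76.6 / 74.5 | 2.3 / 4.1 / 6.3 |
| 1.5, 1 | 99 / 98 / 97 | 80.7 / 80.5 / 80.4 | 0.1 / 0.2 / 0.3 |

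**What the interaction would need.** 80% power on 2 df requires λ = 9.63 (chi-square). Over the four rows with 1 unit at 18 weeks, that means 30 to 78 evaluable per arm, or 38 to 98 after 20% attrition. The planned 64 lies inside this range, but nothing in the plan ties it to this test.

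**The case against.** An omnibus test followed by contrasts is a recognised procedure, and the protocol names the 18-week endpoint. If success requires both steps, a benefit at week 6 alone passes the gate and then fails at 18 weeks. False claims about the primary time point stay near 5%, and with no effect at either visit the joint rate is 2.5%. This stands. A reader might infer that the trial will be declared positive in 75–95% of such cases; that follows only if the interaction itself is taken as the verdict. The text does literally place the significance criterion there, but it does not say that the reading stops there. The fair charge is a success criterion at odds with the endpoint.

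A reader might also infer that the trial is underpowered. The table does not support that in general: the interaction has more power than planned in some scenarios and less in others.

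The 2-df form is an inference, since the coding of time is not stated. The interaction term could be meant as the t2-specific coefficient, but contrasts at both visits come after the significant result, which fits that reading poorly. A linear time term would give a 1-df slope test, which is not the 18-week difference either.

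Finally, the SAP is to set out the contrasts, and mean changes are to be reported whatever the p values. The first leaves the interaction criterion and the condition as the protocol has fixed them. The second is descriptive reporting and does not replace an ungated test.

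**Conclusion.** The concern holds as an inconsistency within {20a} and between {20a} and {14}: the rule that decides significance is neither the primary comparison nor the test on which the trial was sized. Under the assumptions above, an effect confined to week 6 satisfies the interaction criterion in about 75–95% of trials, with about 5% also showing a significant 18-week contrast. When the planned 18-week effect is real, requiring both steps costs between almost nothing and about 10 percentage points, and power depends on a week-6 effect and a correlation that the plan never specifies. The existence of the mismatch does not depend on those assumptions; its size does. It needs correcting because the rule governs the trial's headline conclusion.

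**What to change.** State in {20a} that the primary test is the single prespecified between-arm contrast in DT at 18 weeks, taken from the mixed model with time as a categorical factor. It is tested two-sided at 5%, reported with its 95% confidence interval, and not conditional on the interaction. Make the week-6 contrast and the overall interaction secondary, and carry the same wording into the SAP.

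The cost is wording in the protocol and SAP. Power for this contrast with 64 evaluable per group is the stated 80% (80.1% by the t-test), so neither the 64 nor the 80 per group changes.

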### Interim analyses *{21b}*

No interim analyses will be conducted.

### Methods in analysis to handle protocol non-adherence and any statistical methods to handle missing data *{20c}*

Careful attention will be paid to ensure that all participants are fully assessed at all three study time points to minimise missing data. The study’s research assistant will seek to enter hard copy data to the REDcap database in a timely manner, once time point data is collected. This will provide an opportunity for identification of any missing data, which the research assistant will follow up on by encouraging study participants to try and complete any missing answers. We do not plan to use additional statistical methods such as multiple imputation as studies have demonstrated that linear mixed modelling is mostly sufficient to control for missing data [31, 32]. However, multiple imputation will be considered for any measure with over 5% missing data, using a chained equations method robust to non-normally distributed data. This will be fully reported in line with the updated Consolidated Standards of Reporting Trials (CONSORT) recommendations [33].

### Plans to give access to the full protocol, participant-level data and statistical code *{31c}*

The collated data collected by the investigators will be retained for a maximum of 5 years after the analysis has been completed. We will deliver a completely de-identified dataset on appropriate data upon reasonable request and in agreement with the principal investigator and data protection officer.

### Oversight and monitoring

#### Composition of the coordinating centre and trial steering committee *{5d}*

This is a single-centre study. The trial steering committee will consist of the principal investigator (DB), trial coordinator (SL) and personnel responsible for data entry and data management (CF, YOM and DL). This committee will meet monthly to evaluate the progress of the trial, address ongoing organisational and logistical issues and consider any adverse effects. There will be ongoing communication by way of group email for minor or transient needs. More frequent steering committee meetings will be scheduled should the need arise.

### Composition of the data monitoring committee, its role and reporting structure *{21a}*

During the process of obtaining ethical approval for this single-site study, a Data Protection Impact Assessment (DPIA) screening tool was completed. This was analysed by the hospital’s data protection officer (DPO) in MMUH and the DPO of the Host Institution, University College Dublin (UCD). It was deemed that this study posed a low risk to the rights and freedoms of natural persons and therefore a formal DPIA was not needed. Recruitment of participants is expected to be completed within less than 12 months or once the required number of participants needed is fulfilled. Due to the rapid expected inclusion of participants and the known minimal inherited risks associated with this trial, a data monitoring committee was not appointed.

### Adverse event reporting and harms *{22}*

The study interventions associated with this trial do not involve any physical interventions, and all patients will receive standard of care during their study participation period. Therefore, it is not expected that any participants that volunteer to take part in this trial will suffer from any physical complications as a consequence of participation in this study. However, it is possible that some participants may find the study interventions (psychological therapy, mindfulness and breathing) distressing. This is not expected, but in the event anything arises which is out, it will be reported to the principal investigator. The participant will be removed from the trial if merited and further support will be provided.

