Breathing pattern retraining (BPR) methods activate bodily reactions linked to hyperventilation and can be utilised to facilitate states of relaxation and self-soothing. Some physical sensations from stress and anxiety present as dysfunctional breathing including breathing difficulties, breathlessness and chest pain, symptoms commonly experienced in cancer. Breathlessness is a symptom that features commonly in cancer, particularly in advanced or recurrent disease, and may be linked to breathing dysregulation often posited to be caused by autonomic nervous system disturbances. Drivers of this include fear, stress and anxiety and can lead to autonomic nervous system arousal which leads to an increased ventilatory drive, which in turn leads to altered breathing patterns becoming established and perpetuating the cycle of dysfunctional breathing and anxiety triggers. Given that effective, efficient, responsive and appropriate breathing patterns are influenced by complex interactions between biochemical, biomechanical and cognitive emotional factors, developing a collaborative programme between both physiotherapy and psychology to address all three elements would support its effective management in this patient group. Dysfunctional breathing symptoms can be helped by (i) breathing retraining exercises, (ii) guided relaxation and (iii) mindfulness. We therefore aim to develop an intervention to address physical and psychological symptoms that impact breathing and anxiety [22].

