## Interventions

### Explanation for the choice of comparators *{6b}*

Compassion-focussed therapy (CFT) is a holistic and integrative psychological approach to universal human suffering, which makes it well placed as a psychotherapeutic intervention for cancer patients. It is being combined with breathing pattern retraining (BPR), used in Buteyko methods [23], to activate bodily reactions linked to hyperventilation and show patients how to facilitate their own states of relaxation and self-soothing just by breathing in a better way. The Buteyko method, or Buteyko breathing technique, is a form of physical therapy that proposes the use of breathing exercises primarily as a treatment for respiratory conditions, and the principal investigator (SL) has trained in this breathing method. It is being chosen due to reports of individuals with cancer breathing more rapidly throughout the course of cancer treatment. We aim to examine the effectiveness of this combined intervention in reducing distress intensity 3 months post-intervention. To achieve this, we have designed our trial to compare this approach with a TAU control arm.

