#### Intervention group: compassion-focussed therapy and breathing pattern retraining

The CFT and BPR intervention will be delivered in a group format and will last approximately 90 min per group session. Group sessions will each comprise two segments, one being CFT and the other being BPR. The CFT will seek to emphasise concepts such as practising compassion, fostering self-awareness, self-soothing, mindfulness exercises, reducing self-criticism and practising kindness and inner warmth. The BPR segments will seek to introduce and develop breath work that can aid self-soothing, relaxation and bodily activation. The physicality of the breath work is largely performed by the treating psychologist (SL) but is also assisted by a senior physiotherapist from the Mater hospital by way of training videos that participants can view and use for practice. Further details of each individual session and its content are provided in Table 1.

**Table 1 Tab1:** Layout of the 6-week compassion-focussed therapy and breathing pattern retraining intervention

Session	Summary of sessions
1	Part 1: Breathing pattern retraining education, breathing assessment, simple breath work. Physiotherapy demo in video and simple breath work Part 2: Understanding compassion, CFT explained, model and intervention review; why we need compassion, our tricky brains and defining emotions such as shame, fear and loneliness; Monkey Mind meditation, just noticing our busy minds
2	Part 1: Motivation and our complex brains; understanding motives and emotions—breaking through fear and blocks Part 2: How our thoughts and images affect our minds and brains; breathing patterns—the mind–body connection. Breathing pattern retraining education—exploring the physiotherapy-led exercises
3	Part 1: Compassionate thinking; the 3 components of self-compassion: mindfulness, common humanity and kindness. How this links with soothing breathing Part 2: Dysfunctional breathing and stress; breathing awareness and breathing practices such as tender self-compassion break and affectionate breathing
4	Part 1: Compassionate mind training through imagery—creating your compassionate self Part 2: Creating your compassionate self; breathing pattern retraining techniques and practice combining compassionate imagery

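### The harms section expects no physical complications because it says there is no physical intervention, which the protocol contradicts; physical effects may be under-reported and detection could differ by arm

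*Protocol article*

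**What the plan says.** Adverse event reporting and harms {22} opens with the premise "The study interventions associated with this trial do not involve any physical interventions" and draws a conclusion from it: "Therefore, it is not expected that any participants that volunteer to take part in this trial will suffer from any physical complications". It then allows that participants might find the therapy, mindfulness or breathing distressing, and says that anything arising goes to the principal investigator.

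Other sections describe the breathing component differently:

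- Background and rationale {6a}: "Breathing pattern retraining (BPR) methods activate bodily reactions linked to hyperventilation". The same section says breathlessness is common in cancer, especially when advanced or recurrent, and calls the programme a combination of psychological and mechanical training.
- Explanation for the choice of comparators {6b}: the breathing method "is a form of physical therapy that proposes the use of breathing exercises primarily as a treatment for respiratory conditions", and it is used "to activate bodily reactions linked to hyperventilation".
- Intervention group section: "The physicality of the breath work is largely performed by the treating psychologist", supported by a physiotherapist's training videos for practice.

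On oversight, section {5d} has the steering committee meet monthly and consider adverse effects. Section {21a} explains that no data monitoring committee was appointed, citing minimal risk and rapid recruitment.

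**The concern.** The harms section gives a reason for not expecting physical harm, and the protocol's own account of the intervention contradicts that reason. This matters because the reporting method that follows is event-driven: something has to arise and be noticed before it is reported. If staff and participants are told that nothing physical is being done, a physical symptom during or after breathing practice is less likely to be linked to the trial and mentioned.

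The second issue is comparability. The trial is unblinded, and the intervention arm is seen in group sessions that the control arm does not have. Unprompted reporting tends to follow contact, so a tabulation of events by arm could partly reflect the chance to report them.

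The third is who receives the reports. Two sections attach the principal investigator role to different people, and one of them is the psychologist who delivers the intervention.

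**Working it through.** The plan gives no adverse-event figure, so there is nothing to reproduce. The check compares sections and counts contacts.

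**1. Premise against description.** Section {22} says nothing physical is involved. Section {6b} classifies the method as physical therapy, {6a} and {6b} both state a bodily mechanism, {6a} adds a mechanical component, and the intervention section refers to the physical side of the breath work and to physiotherapy material. In Table 1, five of the six session summaries mention breathing or breath work (sessions 1, 2, 3, 4 and 6). The premise does not fit this description.

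**2. Inference.** The expectation of no physical complications is introduced as following from the premise, together with the fact that all patients receive standard care. Standard care does not bear on what the breathing exercises might do. Without the premise, the expectation has no stated support.

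**3. Capture.** Table 2 lists the Distress Thermometer, PHQ-9, GAD-7, IES-R, Mini-MAC and demographics, with no adverse-event row. Section {18a} lists three data-collection points and no enquiry about events. The route in {22} and the committee review in {5d} both depend on an event having come to notice.

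**4. Planned contacts after baseline during the study period.**

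- Intervention arm: 6 group sessions + 2 assessments (t1, t2) = 8.
- Control arm: 0 group sessions + 2 assessments = 2.

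The assessments are the same in both arms. The difference of 6 is entirely therapist contact.

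**5. Direction of a possible distortion.** The documents give neither an event rate nor a capture rate, so this step is an assumption. Let the true event rate be equal in both arms and let control events be captured at a fraction c of the intervention-arm capture rate. The observed risk ratio is then 1/c:

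- c = 1 gives 1/1 = 1
- c = 0.5 gives 1/0.5 = 2
- c = 0.25 gives 1/0.25 = 4

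This shows only which way unequal contact would push the comparison. It does not estimate what will happen.

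**6. Recipient of reports.** Section {6b} identifies the principal investigator as the person trained in the breathing method, and {11a} identifies that same person as the psychologist delivering the sessions. Section {5d} begins "The trial steering committee will consist of the principal investigator", but gives that role to someone else and lists the psychologist as trial coordinator. Under {6b} the therapist receives the harm reports. Under {5d} another person does, although the therapist still sits on the committee that considers them.

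**The case against.** The strongest reply is that the harms text is broader than its opening sentence. The reporting clause covers anything that arises and is not limited to psychological events or to one arm. Breathing is named as a possible source of distress. The committee considers adverse effects every month, and section {11b} lists significant physical deterioration as a ground for discontinuing the intervention. A reader might infer that physical harms will go uncounted; these provisions do not support that. The supportable statement is that they may be under-reported.

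A reader might also infer that ascertainment will differ by arm. The documents do not say so. The research assistant carries out the same three assessments in both arms and keeps contact with all participants ({18a}, {18b}), and no between-arm comparison of harms is announced. Unequal detection is a possibility that follows from open allocation and the extra sessions, and no more than that.

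It is fair, too, that an article may leave the wording of an adverse-event form to the full protocol. That would be a complete answer if the point were only a missing form. It does not answer a printed premise that other printed sections contradict, nor the event-driven route described alongside it.

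Finally, {6a} presents the bodily reactions as a means to relaxation, says breathing exercises can help dysfunctional breathing, and reports no physical harm. That stands: nothing here shows that the intervention is harmful. The intervention section gives each session two segments but no division of time, so the breathing share cannot be put at a half.

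**Conclusion.** The contradiction is established from the text alone: the no-physical-intervention premise in {22} is incompatible with {6a}, {6b} and the intervention description, and the expectation built on it is unsupported. Possible under-reporting and possible unequal detection are reasonable inferences. They assume that no solicited enquiry exists beyond what the article describes and that the extra sessions give more opportunity to report.

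The size cannot be stated. Zero-event bounds are tempting: with no events, 1 − 0.05^(1/80) = 3.7% for 80 participants and 1 − 0.05^(1/64) = 4.6% for 64. They hold for any fully ascertained sample of those sizes and do not measure this defect. A reader might also suppose that safety is part of the case for national roll-out, but {6a} ties roll-out to reducing distress only.

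The primary estimate, its analysis and the sample size are untouched. What is at stake is how much weight a later statement about harms could bear. The inconsistency over the principal investigator is a separate factual conflict that bears on who receives harm reports. The point is worth correcting because the remedy is cheap.

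**What to change.** 1. Reconcile {22} with {6a}, {6b} and the intervention description by removing the statement that no physical intervention is involved and the inference drawn from it.
2. Have the research assistant ask one short, open adverse-event question covering physical and psychological events, in the same words in both arms, at the existing t1 and t2 assessments. Record the answers on the case report form and tabulate them by arm.
3. Reconcile {6b} and {5d} on who is principal investigator, so that it is clear whether harm reports go to the treating therapist.

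The cost is one form item, one table and two text corrections. No visit is added, because t1 and t2 already take place in both arms.

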### Strategies to improve adherence to interventions *{11c}*

All participants for this trial will be eligible to receive the psychological and breathing interventions (see the ‘Intervention description {11a}’ section). Those in the treatment arm of the study will be offered the intervention immediately after enrolment and those in the control arm of the study will have the option of completing the group programme once the study period has been completed. Additional measures to aid adherence include its virtual format, ensuring there are no geographical barriers precluding someone from participating. Moreover, the group sessions will only last approximately 90 min, inclusive of a break, to minimise the content burden. All participants will also be well-informed during the consent process. The study participation burden, such as completion of primary outcome questionnaires at t(0) (baseline), t(1) (post-6-week group intervention) and t(2) (3 months post-intervention period), post-enrolment will be explained. The research assistant responsible for screening potential study participants will record all eligible candidates and those that do not proceed with the study due to ineligibility, non-consent or withdrawal. In so far as it is possible, only eligible and fully willing individuals will proceed to randomisation and allocation of the patient to either the CFT and BPR or control groups.

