### Provisions for post-trial care *{30}*

All patients, irrespective of group allocation, will receive routine medical management for their cancer recurrence and will be referred for physical therapy on an outpatient basis, or other services, depending on clinical indications and personal needs. All participants that are enrolled into this study are covered by indemnity for negligent harm, through the standard Health Service Executive (HSE) indemnity arrangements. If any participant suffers from any stress or mental health complications arising directly from either intervention during or after the trial, then the participant will be offered further psychological management in line with TAU. This will be offered by a different psychologist that has no direct or indirect involvement with this trial. The research team for this study will liaise with clinical staff attached to the medical teams to make these arrangements.

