### Outcomes *{12}*

#### Primary outcome

Distress Thermometer Likert scale score [time frame: 3 months after completion of the 6-week group intervention]

The Distress Thermometer (DT) assessment tool will be used to assess for psychological distress levels at the appropriate study time points. This assessment will be conducted by the research assistant. Its scale is measured between ‘0’ and ‘10’, where ‘0’ indicated no distress and ‘10’ indicates extreme distress. A decrease on the DT score of 1 unit (standard deviation of improvement of 2 units) is considered clinically significant and can indicate an improvement in a person’s psychological distress levels [13].

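### The harms section lets a participant distressed by the intervention be removed from the trial, with no follow-up afterwards, so distress scores can be lost in one arm only

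*Protocol article*

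**What the plan says.** The harms section {22} of the protocol article acknowledges that "it is possible that some participants may find the study interventions (psychological therapy, mindfulness and breathing) distressing". It adds that this is not expected, that anything arising goes to the principal investigator, and then: "The participant will be removed from the trial if merited and further support will be provided".

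Other sections bear on this rule:

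- **Criteria for discontinuing or modifying allocated interventions {11b}** lists worsening mental health, but as a reason to stop the intervention. It is silent on later assessments.
- **Provisions for post-trial care {30}** says that where stress arises from an intervention, "the participant will be offered further psychological management in line with TAU". It offers care and does not mention outcome assessment.
- **Strategies to improve adherence {11c}**: "those in the control arm of the study will have the option of completing the group programme once the study period has been completed".
- **Statistical methods {20a}** states intention to treat: "all randomised participants will be included in the main analysis and will be analysed as randomised, regardless of protocol adherence".
- **Section {20c}**, on non-adherence and incomplete data, sets this aim: "Careful attention will be paid to ensure that all participants are fully assessed at all three study time points to minimise missing data". That section also relies on the linear mixed model and says multiple imputation will be considered for any measure with more than 5% missing.
- **Retention {18b}** promises contact for as long as a person is participating.

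**The concern.** Stopping a treatment and leaving a trial are different events. Section {11b} describes the first and section {22} the second. Someone removed from the trial has, on the plain wording, no further t1 or t2 assessment, and nothing elsewhere restores it.

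Two features make this more than ordinary attrition:

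- **One arm only.** The trigger is distress caused by the study interventions, which controls do not receive within the 18 weeks. Ordinary dropout and the {11b} criteria can occur in either arm; this route cannot.
- **Related to the outcome.** The primary outcome is a distress score. The people whose scores would be lost are those the intervention may have harmed. The trial is also unblinded, and no criterion is given for when removal is warranted.

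The intention-to-treat statement does not solve this. Scores already recorded still enter the mixed model, so the analysis set is intact. What is lost is follow-up, and an analysis plan cannot recover scores that were never collected.

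**Working it through.** **The plan's own figure.** Sample size {14} assumes a 1-unit difference, SD of change 2, 80% power and two-sided 5% error. A two-sample t-test needs 63.8, so 64 per group (power 0.801), and 64/0.80 = 80. The stated 64 and 80 reproduce. They supply the scale for what follows and are not in dispute.

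**Inputs from the protocol.** 80 randomised per arm, 64 per arm with data, SD of change 2, target 1 unit.

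**Assumptions, because the protocol gives no figures.**

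- *k* of the 80 intervention participants, from 0 to 8, are removed before t1, so only their baseline score is observed.
- Their unobserved 18-week score averages *gap* points above that of the retained participants, with *gap* from 0 to 3.
- SD is 2 at each time and the baseline to 18-week correlation is r = 0.5. This matches the protocol's SD of change: 2 × √(2 × (1 − 0.5)) = 2.
- All other losses are unrelated to outcome.

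**Bias.** Without adjustment, the retained mean understates the full-arm mean by (k/80) × gap. The removed group's baseline is expected to be r × gap higher, and adjusting with slope r recovers r² × gap. So:

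adjusted bias = (k/80) × gap × (1 − r²) = (k/80) × gap × 0.75

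**Error rate.** The adjusted standard error is 2 × √0.75 × √(2/64) = 0.306. With bias b, the two-sided false-positive rate is 1 − Φ(1.96 − b/0.306) + Φ(−1.96 − b/0.306).

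| Gap (DT points) | Removed of 80 | Adjusted bias | False-positive rate |
|---|---|---|---|
| any | 0 | 0 | 5.0% |
| 0 | any | 0 | 5.0% |
| 1 | 8 | 0.075 | 5.7% |
| 2 | 2 | 0.0375 | 5.2% |
| 2 | 4 | 0.075 | 5.7% |
| 2 | 8 | 0.15 | 7.8% |
| 3 | 8 | 0.225 | 11.4% |

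Worked example, gap 2 with 8 removed: (8/80) × 2 × 0.75 = 0.15, and 0.15/0.306 = 0.49, which gives 7.8%.

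**Checks.** A simulation of 8,000 trials (analysis of covariance on baseline, removal driven by a latent variable correlated 0.5 with the 18-week score, 64 completers per arm) gave bias of 0.044, 0.082 and 0.147 and error rates of 5.3%, 5.6% and 7.7% for 2, 4 and 8 removed. These are close to the gap-2 rows. With no baseline adjustment, 8 removed and a 3-point gap give (8/80) × 3 = 0.30.

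**The case against.** The strongest reply is that this is one conditional sentence, in a journal article that condenses a fuller protocol, about an event the authors do not expect. It does not say that assessments stop. Sections {11b}, {20a} and {20c} point towards stopping treatment while assessing and analysing everyone, so the phrase may simply be loose. Detailed follow-up procedures after discontinuation can fairly be left to the full protocol.

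Part of this stands. Silence in {11b} alone would be missing detail and no finding. But {22} makes a positive statement, and it works against the general aims in {20a} and {20c}. Neither of those addresses a person who has been removed.

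The second reply concerns direction and size. Removal would come around a 6-week course, while the outcome is measured 12 weeks after it and extra support is promised in between. Session distress may have passed by then, and the gap could be zero. This stands: bias towards benefit requires that removed participants would have scored worse. For 4 or fewer removals at a 2-point gap the effect is small, and the upper figures need 10% of the arm removed before t1.

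Third, the mixed model, or imputation above 5% missing, offers some protection. It does, but both normally assume that observed data explain the missingness. Distress that emerges in the sessions and leads to removal before t1 appears in no recorded score except baseline. If t1 is observed, the bias is smaller but not necessarily nil.

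Finally, distressed participants may decline questionnaires whatever the wording, so the fix recovers only part of the loss.

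**Conclusion.** The concern holds. Followed as written, section {22} can lose distress outcomes in the intervention arm alone, for a reason tied to the primary outcome, and nothing in the article prevents it. The likely direction favours the intervention.

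The size is uncertain and may be nil. It depends on assumed removal numbers and an assumed gap, neither of which the protocol informs. At a 2-point gap, 0 to 8 removals cost 0% to 15% of the 1-unit target. The most extreme case shown, 8 removals with a 3-point gap, is 0.225 units adjusted. This does not undermine the design. It is an avoidable risk that should be corrected because lost scores cannot be recovered later and the correction is cheap. Confidence is medium, since the harm depends on how often the rule is used and how literally it is read.

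**What to change.** Reword section {22} so that distress or worsening leads to stopping the intervention and offering the support already described in {30}, while t1 and t2 questionnaires continue unless the participant withdraws consent to data collection. Add the same clarification to {11b} so that the two sections agree. Clinical discretion and reporting to the principal investigator stay as they are.

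The cost is one or two sentences of protocol wording and a few extra questionnaires from distressed participants, who remain free to decline. The sample size does not change. The article reports 8.5% of patients recruited, so an amendment at that stage would have covered most of the trial.
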